### 6.1.5. Analyses of secondary outcomes

Analyses of continuous/ordinal secondary outcomes will be done in the same way as described above: first unadjusted comparison of groups means using t-tests, then ANCOVA comparisons of group means adjusting for baseline values of the outcome, and finally regression analyses which adjust for additional baseline variables. Depending on the response rates at month 4 (and whether these rates are similar in control and intervention groups), we may also compare group means using mixed-model HLM analyses.

For yes/no outcome variables, such whether or not a subject quit his/her job during follow-up, we will compare the percentages yes in the control and intervention group first using a chi-square test to do an unadjusted analysis. We will then use logistic regression to do an ANCOVA type analysis which adjusts only the baseline of the outcome. Lastly we will do adjusted logistic analyses which control for other baseline variables.

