## 2.2. Secondary questions

Secondary outcomes will include:

1. At 4 months post-randomization
   1. depression severity as measured by K6
   2. client satisfaction　[VAS for satisfaction with the company’s support for mental stress, and a detailed ad hoc questionnaire for those who received telephone CBT]
2. At 15 months post-randomization
   1. depression severity [BD12 and K6]
   2. work performance
      1. “Effective hours worked” for the past month [HPQ]
      2. Job retention: has the person quit his/her job by 15 months post-randomization [yes/no, if yes when did the participant quit the job? The latter information is important for survival analysis.]
   3. client satisfaction [VAS]
   4. use of EAP services, use of health services (physical or mental), suicidal attempt, hospitalization (physical or mental) [yes/no for 15 months post randomization]
   5. time to incident major or minor depressive episode during the 15 months post randomization

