### 6.1.4. Analyses of Primary Outcomes

Our two primary outcomes are the BD12 measure of depression severity and the HPQ measure of effective hours worked, both assessed at the month 4 follow-up. Both of these measures are continuous/ordinal variables so will compute the mean BD12 and mean HPQ at month 4 in the two groups, control and intervention.

We will first do unadjusted analyses to compare the means using a t-test. We will then do several adjusted analyses. First will use ANCOVA to compare the month 4 means on the outcome adjusting for baseline differences on the outcome. ANCOVA is simply another term for regression. For example, in one model, BD12 at month 4 will be the outcome and treatment group (a 0/1 variable) and baseline BD12 will the independent variables. These ANCOVA analyses provide estimates of "adjusted" month 4 group means as well as estimates of the adjusted difference in the group means (along with a p-value and confidence interval for the difference).

We will also do adjusted analyses which control for additional baseline variables, including variables which differ significantly between the control and intervention groups and variables which are strong predictors of the outcome under analysis. We will compare the estimated difference in group means and p-values to those obtained from the unadjusted analysis and the ANCOVA analyses which adjusts only for the baseline value of the outcome.

These analyses will be restricted to subjects who complete the month 4 follow-up (all of the statistical methods described above drop from the analysis those with a missing value on the outcome). Since a true intent-to-treat analysis estimates treatment effects based on data from all randomized subjects, not just those who complete a given follow-up, we will also do some mixed-model hierarchical linear models (HLM) to estimate treatment effects based on all subjects. NOTE: If the response rate is high at the month 4 follow-up (say at least 90%), bias due to missing data will likely be quite small and these analyses may not be necessary.

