### 6.1.5. Analysis of non-response

We will do analyses to compare the baseline characteristics of subjects who complete the month 4 follow-up and subjects who do not complete the month 4 follow-up (completers and non-completers). We want to know if those who do not complete the month 4 follow-up differ in important ways from those who do. For example, it would be important to know if the non-completers have more severe depression at baseline. If so, non-completion would be more likely to bias the results, particularly if the completion rates differ between control and intervention.

For all of our variables in Table 1, we will compute means and percentages of the completers and non-completers for each treatment group at baseline. We will use t-tests to compare the means for continuous/ordinal variables in the completers and non-completers. For yes/no variables, we will compare the percentages in these two groups using a 1 d.f. chi-square test.

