## 6.2. Termination policy

We are planning a recruitment phase of 9 months (extendable up to 12 months). We will then start the 1-year follow-up, to be implemented at 15 months after randomization for both the treatment and waiting list groups.

After this 15-month follow-up evaluation, those in the waiting list group who wish to receive telephone CBT can receive telephone CBT.

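### The mixed-model trigger and the non-response check for the continuous month-15 outcomes look at month-4 response, so month-15 loss could go unadjusted and unexamined

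*Protocol*

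**What the plan says.** Section 2.2 lists two secondary headings at month 4 (K6 and satisfaction) and five under "At 15 months post-randomization". The continuous month-15 items are BDI2, K6, HPQ effective hours and the satisfaction VAS. The others are yes/no or time-to-event, such as job retention, service use and "time to incident major or minor depressive episode during the 15 months post randomization".

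Section 6.1.5 (Analyses of secondary outcomes) treats continuous secondary outcomes like the primaries: t-test, ANCOVA on the baseline value, then regression with further covariates. Section 6.1.4 acknowledges that these methods lose anyone whose outcome is missing. The one route to an all-subjects analysis is introduced by "Depending on the response rates at month 4 (and whether these rates are similar in control and intervention groups" and continues "we may also compare group means using mixed-model HLM analyses". Month-15 response is not mentioned.

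For the primary outcomes, section 6.1.4 gives the reason for waiving the mixed model: "If the response rate is high at the month 4 follow-up (say at least 90%), bias due to missing data will likely be quite small". The mixed model described there has at most two records per person, baseline and one follow-up, with slopes running to month 4.

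The section on analysis of non-response opens "We will do analyses to compare the baseline characteristics of subjects who complete the month 4 follow-up" and extends to no other visit.

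Section 3.2 expects 90% to complete month 4 and gives no figure for month 15. It states that month 15 is underpowered and exploratory, and that its purpose is to inform a later trial of prophylactic effect.

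**The concern.** Both safeguards against missing data look at a visit 11 months before the outcomes they should protect. The protocol's own reasoning is that a high response rate keeps bias small, and that unequal completion between arms makes bias more likely. Each argument concerns the visit being analysed. A full and balanced month-4 return establishes neither for month 15.

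The situation is plausible. The planned month-4 return equals the level at which section 6.1.4 regards the mixed model as possibly unnecessary. Response by arm could also separate later: the CBT arm has long finished, while for controls "After this 15-month follow-up evaluation, those in the waiting list group who wish to receive telephone CBT can receive telephone CBT".

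If the mixed model were used, its two-record form would take baseline and month 15 and ignore the month-4 score already held for someone who misses month 15. That score is probably the best available predictor of both the missing value and the loss. At stake is the month-15 estimate that is meant to inform the next trial.

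**Working it through.** **1. The plan's own figures.** With 1:2 allocation, two-sided 0.05 and d = 0.40, 90% power needs 99 in the intervention arm, as stated; power with 99 and 198 is 0.901. After 90% response (99 × 0.9 ≈ 89; 198 × 0.9 ≈ 178), power at 0.42 SD is 0.899, as stated. For 0.16 SD, power is 0.23 at 90% response and 0.17 at 60%, which agrees with the protocol's remark on month 15. The sample size is not in dispute.

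**2. Which outcomes the trigger reaches.** It concerns comparisons of group means, so of the month-15 items it covers BDI2, K6, effective hours and the VAS. Yes/no outcomes get chi-square and logistic regression, outside the trigger.

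**3. Hand formula for unadjusted respondent-only bias.** Let m be the non-response rate in an arm and g the amount in SD by which non-respondents are worse than respondents. If g is the same in both arms, bias in the benefit (control minus CBT) = (m_CBT − m_control) × g.
- Non-response 30% v 20%, g = 0.3 to 0.8: 0.10 × 0.3 = 0.03 to 0.10 × 0.8 = 0.08 SD.
- Equal rates and equal g: zero.
- Equal rates of 20% but g larger by 0.5 SD in one arm: 0.20 × 0.5 = 0.10 SD.

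Baseline adjustment removes part of this.

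**4. Simulation with baseline adjustment.** From section 3.2: effects of 0.42 SD at month 4 and 0.16 SD at month 15, and 1:2 allocation. Assumed: correlations 0.5 (baseline to month 4), 0.4 (baseline to month 15) and 0.6 (month 4 to month 15); month-4 response 92%; the month-15 response rates below; log-odds of loss rising 0.7 per SD of month-4 depression where stated. Samples were very large, so the departures from 0.16 are essentially bias. Ranges are over repeated runs.

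| Month-15 response, CBT v control | Loss depends on month-4 score in | Respondent-only ANCOVA | Bias (minus 0.16) |
|---|---|---|---|
| 70% v 85% | both arms | 0.195–0.202 | +0.035 to +0.042 |
| 70% v 85% | CBT arm only | 0.233–0.237 | +0.073 to +0.077 |
| 70% v 80% | control arm only | 0.105–0.11 | −0.055 to −0.05 |
| 80% v 90% | both arms | 0.185 | +0.025 |
| 80% v 85% | CBT arm only | 0.211 | +0.051 |
| 5-point gap | both arms | 0.171–0.175 | +0.011 to +0.015 |
| 75% v 75% | both arms | 0.156–0.165 | nil within simulation error |

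A baseline-plus-month-15 model gave the same values as ANCOVA where both were run (0.203, 0.237, 0.105 and 0.165 for the first three rows and the last). Estimation that also used the month-4 score gave 0.153 to 0.167.

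**5. Scale.** SE at 70% v 85%: residual variance 1 − 0.4² = 0.84; respondents 99 × 0.70 = 69.3 and 198 × 0.85 = 168.3; SE = √[0.84 × (1/69.3 + 1/168.3)] = 0.131 SD. A bias of 0.077 is 0.077/0.16 = 48% of the expected effect and 0.077/0.131 = 0.59 SE. A bias of −0.055 is 34% of the effect and 0.42 SE.

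**The case against.** **Nothing forces a respondent-only analysis.** A reader might infer that a month-4 return above 90% commits the trial to respondent-only month-15 comparisons. The text does not support that. The 90% figure belongs to the primary outcomes and is itself loose; the secondary section sets no threshold and says only that the model may be used. This stands: the outcome is possible, not certain.

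**The trigger does not govern most secondary outcomes.** A reader might also infer this from the number of month-15 headings. It does not follow, because many of those items are yes/no or time-to-event. This stands and limits the scope.

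**Month 15 is exploratory and underpowered.** Effectiveness is decided on the two month-4 primaries, and even the larger biases above are under 0.6 SE. This stands and limits the weight. It does not remove the point, because informing a later trial is the stated reason for month 15, and a systematic error would carry forward into it.

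**Unequal loss is conjecture.** Retention effort is the same in both arms (cards, postcard, second mailing, telephone call), month-15 data are sought after stopping the intervention, and the DSMB sees completion at each follow-up. All true, and the 70% v 85% case is no natural default. But none of these is an analysis rule.

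**Naming the visit analysed would be enough.** That would correct the reference, and further modelling detail may sit in an SAP. It would still leave a two-record model that gives no protection against loss driven by month-4 status.

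**Conclusion.** The point holds for the continuous month-15 outcomes. It is a stated rule that refers to the wrong visit, not a detail left for later. As written, those comparisons could rest on respondents only, with no planned examination of month-15 loss, and the described mixed model would not use the month-4 scores.

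The size is conditional. Rounded outward, bias is about -0.06 to +0.08 SD against an expected 0.16 SD when response differs by 10 to 15 points and loss is related to month-4 depression. It is about 0.01 to 0.015 SD with a 5-point gap and the same loss pattern in both arms, and nil when both rate and pattern are equal. Material bias therefore needs a large response gap or a loss pattern that differs by arm. Month-15 response, correlations and loss mechanism are all assumptions; the protocol supplies none.

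A reader might infer that the trial's main conclusion is at risk. It is not: the primary decision is made at month 4. The change is worth making because it is cheap, not because the consequence is grave.

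**What to change.** In section 6.1.5 (Analyses of secondary outcomes), remove the month-4 response condition for month-15 outcomes. For BDI2, K6 and effective hours, estimate the month-15 difference from a repeated-measures model with baseline, month 4 and month 15 as responses, arm-by-visit means and unstructured covariance, on all randomised participants and whatever the month-4 response.

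In the section on analysis of non-response, repeat the completer v non-completer comparison for month 15, by arm, and add the month-4 BDI2, K6 and HPQ scores to the variables compared.

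The satisfaction VAS is not among the listed baseline measures, so this model does not cover it; removing the trigger and adding the month-15 non-response comparison still apply. The yes/no and time-to-event outcomes lie outside both the trigger and the model.

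The cost is wording in two paragraphs and one extra model per outcome, with no new data. The model assumes data missing at random given baseline and month 4, which is weaker than what the respondent-only ANCOVA assumes.

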### 3.1.1. Inclusion criteria

1. Age 20-57 at study entry [because the retirement age is usually 60, we have to recruit the patients well before 60 in order to allow time for follow-up]
2. Men and women
3. Currently employed full-time (either regular or temporary) by the business company
4. Expected to be employed full-time for 2 years after screening
5. K6 scores greater than or equal to 9 (or 10) at screening
6. BDI2 scores greater than or equal to 10 at 2^nd^ screening (CIDI interview)

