### 3.1.2. Exclusion criteria

1. Part-time employees
2. Sick leave for 6 or more days for a physical or mental condition in the past month
3. Expected to be on pregnancy leave, maternity leave or nursing leave within 2 years after screening
4. Current treatment for a mental health problem from a mental health professional
5. Major depressive episode in the past month, as ascertained by CIDI [We do not exclude dysthymia or major depression in partial remission]
6. Lifetime history of bipolar disorder, as ascertained by CIDI
7. Any substance dependence in the past 12 months, as ascertained by CIDI. [We do not exclude substance abuse.]
8. Any other current mental disorder if it constitutes the predominant aspect of the clinical presentation and requires treatment not offered in the project

We will have a registry of all the candidates at Office X and Factory Y (approximately 1200 regular or temporary employees altogether) of this company to whom we will send the invitation letter, and compare those who give the full consent to participate in the intervention trial to the original population, to examine the generalizability of our results.

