#### 15-month follow-up

Both the intervention group and the control group will receive questionnaires at 15 months post randomization.

The CRC will first send out a notification postcard two weeks before actually sending out the questionnaires. Then the questionnaires will be mailed to the participants. If no response is received within 2 weeks, a second set of questionnaires with an appropriate cover letter will be mailed. If no response is still unavailable, CRC will call the participants, both in the active treatment or control groups.

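### In section 6.1.5 the baseline adjustment is empty for job quitting, no method suits the time-to-event outcomes, and incident minor episode has no at-risk set

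*Protocol*

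**What the plan says.** Section 2.2 lists job retention at 15 months as yes/no with the date of leaving, and says of that date: "The latter information is important for survival analysis". It also lists "time to incident major or minor depressive episode during the 15 months post randomization".

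Section 6.1.5 (Analyses of secondary outcomes) knows two outcome types. Continuous or ordinal outcomes get t-tests, ANCOVA, wider regression and possibly mixed models. For the other type it says: "For yes/no outcome variables, such whether or not a subject quit his/her job during follow-up, we will compare the percentages yes", using a chi-square test. Then: "We will then use logistic regression to do an ANCOVA type analysis which adjusts only the baseline of the outcome". Finally: "Lastly we will do adjusted logistic analyses which control for other baseline variables".

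On entry, section 3.1.1 requires: "Currently employed full-time (either regular or temporary) by the business company". Section 3.1.2 excludes a major depressive episode in the past month but adds: "We do not exclude dysthymia or major depression in partial remission". It does not exclude a current minor episode.

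The 15-month follow-up text in section 5.3.1 says: "Both the intervention group and the control group will receive questionnaires at 15 months post randomization". Section 5.3.4 speaks of CIDI interviews at baseline and at 15 months. Section 3.2 declares the 15-month analyses exploratory.

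**The concern.** The methods in section 6.1.5 do not match the outcomes defined in section 2.2.

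- The baseline-adjusted logistic step adjusts for nothing in the one example the section gives. For suicide attempt and hospitalisation, the baseline lists in section 3.3.2 hold no corresponding variable.
- Job quitting, with its date, is handled as yes/no. Time to incident episode belongs to neither outcome type.
- A person already in a minor episode at entry cannot have an incident minor episode, yet the protocol does not say who is at risk.
- The follow-up section leaves out the interview on which the episode outcome depends.

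Hypothesis 1 in section 1 includes preventing episodes. The economic argument there values preventing 0.1 resignation at $8000 a year. Section 3.2 justifies the 15-month follow-up as groundwork for a later trial of prophylaxis. If model and at-risk set stay open, they can be chosen after the data are seen, and the estimates are a weaker guide to that next trial.

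**Working it through.** **1. The plan's own figures.** The protocol gives none for job retention or incident episode. Its sample size concerns the month-4 outcomes and reproduces (two-sided 5%, sidedness assumed), with power = Φ(d·√(n₁n₀/(n₁+n₀)) − 1.96):
- 99 vs 198, d = 0.40: 0.40 × √66 = 3.25, Φ(1.29) = 90.1%.
- 89 vs 178, d = 0.42: 0.42 × √59.33 = 3.235, Φ(1.275) = 89.9%.

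Nothing below alters these.

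**2. The constant baseline.** The prescribed model is logit(p) = β₀ + β₁·treatment + β₂·baseline. Under section 3.1.1 nobody has quit at entry, so baseline takes one value, c, for all 297. The model becomes logit(p) = (β₀ + β₂c) + β₁·treatment. The design matrix has 3 columns and rank 2, so β₂ is not identified but β₁ is, and it is the unadjusted log odds ratio.

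Illustration with simulated data (5/99 vs 20/198 quitting, assumed risks of 5% and 10%): ln[(5/94)/(20/178)] = −0.748. The logistic fit without the baseline column gives −0.748. With a redundant constant column it gives −0.747, a numerical difference only.

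**3. What a time-to-event analysis would gain.** Simulated power, 3,000 runs per row and dropout level, 99 vs 198, exponential times over 15 months. Event risks, hazard ratios and uniformly timed dropout are assumptions. Chi-square uses only people followed to month 15. Cells show log-rank / chi-square, in %.

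| Control 15-month risk | HR | No dropout | 10% dropout | 20% dropout |
|---|---|---|---|---|
| 5% | 0.5 | 12.7 / 12.7 | 12.1 / 11.6 | 12.4 / 10.6 |
| 10% | 0.5 | 28.3 / 28.3 | 26.6 / 24.7 | 24.6 / 22.4 |
| 20% | 0.5 | 55.3 / 55.9 | 51.7 / 50.5 | 50.3 / 46.7 |
| 30% | 0.5 | 73.9 / 74.3 | 71.6 / 69.8 | 70.3 / 66.3 |
| 30% | 0.6 | 50.8 / 51.2 | 49.9 / 48.1 | 46.9 / 42.0 |

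The gain from log-rank is nil without dropout, 0.5 to 1.9 points at 10%, and 1.8 to 4.9 points at 20%. The chi-square arm drops everyone lost early, even after an event, so the gap would be smaller if such quits were known and counted.

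**4. The at-risk set.** Section 3.1.1 asks for K6 of at least 9 (or 10) and BDI2 of at least 10. Section 3.1.2 removes only a major episode in the past month. The share entering in a minor episode, f, is not given. With at-risk = n(1 − f):
- f = 10% (assumed): about 89 vs 178, with 30 of 297 not at risk.
- f = 25% (assumed): about 74 vs 149, with 74 not at risk.
- f = 50% (assumed): about 50 vs 99, with 149 not at risk.

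This applies to the minor component only. Everyone remains at risk of a major episode.

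**5. The CIDI schedule.** Section 5.1 gives follow-up times for BDI2, HPQ and K6 but none for the CIDI. The 15-month text in section 5.3.1 describes mailed questionnaires and telephone chasing. Section 5.3.4 presupposes a 15-month CIDI. The interview is planned, but the follow-up section omits it.

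**The case against.** A reader might infer that job retention cannot be analysed, or that the adjusted model is non-estimable. The documents do not support that. A constant covariate is redundant: software drops it and the treatment estimate is unbiased. The chi-square test precedes this step, and a logistic model with other baseline variables follows it. Both are sound for a yes/no outcome over a fixed 15 months in both arms, and the later model could already hold the randomisation factors.

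A reader might also infer that follow-up time is thrown away. Section 2.2 collects the quit date for survival analysis, so the intention is on record, and model detail may properly sit in an SAP that is not shown. That stands as a defence against a charge of missing detail. It does not remove the mismatch: section 6.1.5 fixes methods, names job quitting as its yes/no example, and offers nothing that fits a censored time.

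A third tempting reading is that prevalent minor episodes will be counted as incident. The protocol says incident, nowhere says prevalent cases will count, and collects CIDI mood data at baseline. What stands is narrower: the at-risk set is undefined.

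Nor can one say that the 15-month CIDI is missing from the plan; section 5.3.4 shows otherwise. Finally, section 2.1 rests the decision on effectiveness on the two month-4 outcomes, and section 3.2 concedes inadequate power at month 15. That limits the importance of the point.

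**Conclusion.** The point holds as a mismatch between defined outcomes and stated methods. The baseline-adjusted logistic step is vacuous for job quitting and has no listed covariate for suicide attempt or hospitalisation. No stated method suits time to incident episode or uses the quit dates. Incident minor episode has no at-risk set.

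The expected gain from correction is modest: about 0 to 5 power points under assumed dropout of 0 to 20% and the assumed event rates. The 30 to 149 people not at risk of an incident minor episode rest wholly on an assumed 10 to 50%; the gap in definition does not depend on that figure. The chi-square result for job quitting remains valid, provided loss to follow-up is unrelated to quitting. The outcomes are secondary and the 15-month analyses exploratory. The primary analysis and sample size are unaffected. It is worth correcting because these are stated methods that can be changed at almost no cost.

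**What to change.** 1. For yes/no outcomes whose baseline is constant or unmeasured, replace the baseline-of-outcome term in section 6.1.5 with the randomisation factors of section 3.3.4: BDI2 stratum, presenteeism stratum and site.
2. Analyse job retention and time to incident episode by log-rank and Cox regression, stratified or adjusted by the same factors and censored at last contact. State the assumption that loss is unrelated to the event. Keep chi-square as a supporting analysis for job quitting. If events are few, adjusting with 1 + 1 + 2 = 4 terms is safer than 12 strata. At 10% control risk and HR 0.5 (assumed), expected events are 198 × 0.10 + 99 × (1 − 0.9^0.5) = 19.8 + 5.1, about 25, or two per stratum.
3. Keep the prespecified composite of major or minor episode, but count incident minor episodes only among those without minor depression on the baseline CIDI. Report first major episode separately for all participants.
4. List the CIDI in the 15-month follow-up text so that it agrees with section 5.3.4.

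The cost is wording and standard programming. Quit dates and both CIDI interviews are already planned.
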